## **4. Objectives**

### **Primary**

1. To assess the effect of HCQ in reducing SARS-CoV-2 viral shedding by PCR in infected pregnant women with mild symptoms.
2. To assess the efficacy of HCQ to prevent incident SARS-CoV-2 infection in pregnant women in contact with an infected or suspected case.
3. To evaluate the effect of HCQ in preventing the development of the COVID-19 disease in asymptomatic SARS-CoV-2-infected pregnant women.

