#### Trial design

The trial has been designed as a randomized double-blind placebo-controlled multicentre trial to evaluate the safety and efficacy of HCQ to prevent and/or minimize SARS-CoV-2 infection during pregnancy. A total of 714 pregnant women are expected to participate in the study (see sample size calculation).

The study participants will be stratified by clinical presentation and SARS-CoV-2 PCR results. The following are the study groups:

- **SARS-CoV-2-PCR confirmed, infected** pregnant women:
  - a. *symptomatic* (n=100)
  - b. *asymptomatic* (n=100)
- **SARS-CoV-2 PCR negative** pregnant women in **contact** with a SARS-CoV-2-infected confirmed or suspected case (n=514).

Women in each group will be randomly allocated to receive either HCQ or placebo. Evaluations will include safety and tolerability, SARS-CoV-2 PCR and COVID-19 clinical diagnosis and presentation, as well as neonatal SARS-CoV-2 by PCR and IgM/IgG.

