#### *Inclusion criteria*

Women will be invited to participate in the trial and sign an informed consent if they meet the following inclusion criteria.

- Presenting with fever ( $\geq 37.5^{\circ}\text{C}$ ) and/or one mild symptom suggestive of COVID-19 disease (cough, dyspnoea, chills, odynophagia, diarrhoea, muscle pain, anosmia, taste disorder, headache) OR contact of a SARS-CoV-2 confirmed or suspected case in the past 14 days
- More than 12 weeks of gestation (dated by ultrasonography)
- Agreement to deliver in the study hospitals

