## **b. Definitions**

### **Contact**

According to the WHO and the European Centre for Disease Prevention and Control (ECDC) a contact of a COVID-19 case is any person who has had contact with a COVID-19 case (Annex 2) within a timeframe ranging from 48 hours before the onset of symptoms of the case to 14 days after the onset of symptoms (22).

If the case had no symptoms, a contact person is defined as someone who has had contact with the case within a timeframe ranging from 48 hours before the sample which led to confirmation was taken, to 14 days after the sample was taken. The associated risk of infection depends on the level of exposure.

Since local and community transmission has been reported in Spain and in the study areas, all patients presenting with symptoms of acute respiratory infection in primary care or the emergency department of a hospital (first contact with the healthcare system) will be considered as suspected cases.

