#### **Statistical analysis populations**

The assignment of participants into analysis populations will be performed prior to database lock and any data analysis. The following populations are defined:

a) Intention to treat (ITT)

This population will include all randomized pregnant women and will be the target population for the efficacy analysis. Following the intention-to-treat principle, patients will be analyzed according to the treatment they were assigned to at randomization.

b) According to protocol (ATP)

This population will include all women who fulfil all the inclusion-exclusion criteria, took the 14 days HCQ treatment and from whom data is available for the analysis.

c) Safety

This population will include all patients who received at least one dose of HCQ/placebo and had at least a follow-up visit. The participant's safety will be analyzed by trial arm.

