#### **Statistical models and methods of analysis**

The primary analysis of the trial will be:

- The comparison of the proportion of negative SARS-CoV-2 PCR at day 14 after initiating treatment administration among those women who were SARS-CoV-2 PCR positive at recruitment in the ITT and ATP cohorts.
- The comparison of the proportion of pregnant women who were negative SARS-CoV-2 PCR at recruitment and close contacts of confirmed cases of SARS-CoV-2 infection, with a positive PCR for the infection at day 14, in the ITT and ATP cohorts.

Proportions will be compared between the two intervention-arms within each group using the Fisher exact test and presented as relative risk ratio (RR) or reduction of the RR ( $1 - RR * 100\%$ ) if RR lower than 1. Adjustment for co-variables and possible confounders will be done using Poisson regression with a log link and robust estimate of the covariance (Huber method), using the method proposed by Zou et al. 2014 and 2013.

Continuous variables will be compared between groups using Wilcoxon rank sum test and the effect presented as Mean Difference. Adjustment for co-variables and possible cofounders will be done using ordinary least square regression. Variables will be transformed to the logarithm scale if normality is improved and results presented as Proportional Difference. If after transformation, non-normality of the residuals is detected using diagnostic regression plots, robust intervals of confidence and Wald test will be presented instead.

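### The primary prevention analysis names only close contacts of confirmed cases, which contradicts objective 2, the randomised contact group and the ITT definition, all of which take in contacts of suspected cases

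*Protocol*

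**What the plan says.** Most of the Protocol describes one prevention population.

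- Objectives, Primary, item 2: "To assess the efficacy of HCQ to prevent incident SARS-CoV-2 infection in pregnant women in contact with an infected or suspected case".
- Inclusion criteria: a woman may enter as a "contact of a SARS-CoV-2 confirmed or suspected case in the past 14 days".
- Trial design: the third study group is PCR-negative women in contact "with a SARS-CoV-2-infected confirmed or suspected case (n=514").
- Randomization, Study groups: asymptomatic PCR-negative women who are contacts of either kind of case form the uninfected contact group. Symptomatic PCR-negative women stay in the study only if they report such a contact.
- Statistical analysis populations, on ITT: "This population will include all randomized pregnant women and will be the target population for the efficacy analysis".

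Statistical models and methods of analysis then describes the second primary comparison. It concerns women who were PCR-negative at recruitment and were "close contacts of confirmed cases of SARS-CoV-2 infection, with a positive PCR for the infection at day 14". The sentence ends by placing the comparison in the ITT and ATP cohorts.

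The definition of a suspected case is wide. Because of community transmission, it takes in "all patients presenting with symptoms of acute respiratory infection in primary care or the emergency department of a hospital", at first contact with the healthcare system. The Definitions section defines a contact, but not a close contact.

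**The concern.** The sentence that fixes the primary prevention comparison describes a narrower group than the one enrolled and randomised. It narrows in two ways: suspected index cases disappear, and an undefined qualifier (close) is added. The Protocol does not explain the narrowing, does not say how randomised contacts of suspected cases would be analysed, and does not enlarge the sample to allow for leaving them out.

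Two things are at stake. First, an analyst could take the primary population to be all 514 women or an unspecified subset, and a confirmatory analysis should not leave that choice open. Second, the prevention sample size has no reserve, so a smaller analysis set could cost power. How much depends on facts that the Protocol does not give.

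**Working it through.** **Step 1. The passages side by side.**

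| Place in the Protocol | Contacts of confirmed cases | Contacts of suspected cases |
|---|---|---|
| Objective 2 | included | included |
| Inclusion criteria | included | included |
| Trial design, group with n=514 | included | included |
| Randomization, Study groups | included | included |
| ITT population | included (all randomised) | included (all randomised) |
| Primary prevention comparison | included, if close | not mentioned |

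Only the last row differs. It is also at odds with itself: it limits the women by type of exposure and in the same sentence cites a cohort that has no such limit.

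**Step 2. Reproducing the planned sample size.** Inputs from Sample size: control rate 3%, a reduction of 3 percentage points (so 0% on treatment), 80% power, two-sided 0.05. Allocation is 1:1. With pooled rate p = (0.03 + 0)/2 = 0.015, the usual formula is

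n = [1.960 × √(2 × 0.015 × 0.985) + 0.842 × √(0.03 × 0.97 + 0)]² / 0.03²

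= (0.3369 + 0.1436)² / 0.0009 = 256.5, so 257 per arm.

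The stated 257 is reproduced exactly. Normal-approximation power at 257 is 80.1%, so nothing is held in reserve.

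**Step 3. Power with the planned test.** The Protocol compares proportions with Fisher's exact test. With no infections on treatment, the two-sided p-value at 257 per arm is 0.061 for 5 control infections and 0.030 for 6. Significance therefore needs at least 6 control infections, and the same threshold applies at every smaller size used below. Power is

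P(X ≥ 6), with X binomial (n per arm, control rate).

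At n = 257 and 3% this is 78.5%.

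**Step 4. If contacts of suspected cases were left out.** The Protocol gives neither their share nor a separate infection rate. Let f be the share of contacts kept (assumed). Take the planning rate of 3% as the rate for the whole mixed group, and let s be the control rate among contacts of suspected cases. The control rate among those kept is then

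(0.03 − (1 − f) × s) / f.

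The table gives Fisher power against 0% for three values of s. All three are assumptions.

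| Left out | n per arm | s = 3% (kept women at 3%) | s = 1% | s = 0% (all infections among those kept) |
|---|---|---|---|---|
| 0% | 257 | 78.5% | 78.5% | 78.5% |
| 10% | 231 | 69.4% | 75.7% (rate 3.22%) | 78.4% (rate 3.33%) |
| 20% | 206 | 58.6% | 73.0% (rate 3.50%) | 78.8% (rate 3.75%) |
| 30% | 180 | 45.5% | 69.7% (rate 3.86%) | 78.7% (rate 4.29%) |
| 40% | 154 | 31.7% | 66.1% (rate 4.33%) | 78.7% (rate 5.00%) |

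With s = 0 the expected number of control infections stays at 257 × 0.03 = 7.7 whatever share is left out, which is why power hardly moves. With s = 3% it falls to 154 × 0.03 = 4.6 at 40% left out, below the 6 that are needed.

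**The case against.** The best reply is that the phrase is loose shorthand. The same sentence cites the ITT cohort, which is all randomised women, and the next paragraph compares arms within each study group, where the contact group is the full 514. No passage says that contacts of suspected cases are excluded. The Synopsis is similarly loose: it first calls the 514 contacts of a case, then speaks of contacts of suspected or confirmed cases. The section also presents itself as a general outline, with a data analysis plan to follow.

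Much of this stands. A reader might infer that the plan definitely drops randomised women, but the documents support only the conditional statement that it does so if the sentence is taken literally. A reader might also infer that power certainly falls, possibly to about a third. That requires contacts of suspected cases to be infected as often as contacts of confirmed cases. If they are infected less often, the loss shrinks, and at the limit it vanishes. The sample size paragraph does not settle this, since it speaks only of uninfected women with a contact and does not split by index case.

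Two further inferences lack support. The wide definition of a suspected case makes a large share conceivable, but no share is given. Nor does any passage describe revising index-case status after randomisation; the Protocol merely does not say when that status is fixed.

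What does not stand is that nothing needs doing. The sentence is the Protocol's own statement of a primary comparison, and it disagrees with the objective it serves. A later analysis plan could choose either reading, so the Protocol text should be aligned in any case.

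**Conclusion.** The contradiction is established from the text alone and needs no assumption: the primary prevention comparison is worded for a narrower group than objective 2, the randomised contact group and the ITT definition. It may be a drafting slip. Left as it is, it makes the primary population ambiguous, and under the literal reading the result would not answer objective 2 for all the women enrolled under it.

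The effect on power is conditional and cannot be reduced to one figure. With 40% of contacts left out, Fisher power for 3% versus 0% overall lies between about 32% and 79%, against 78.5% with everyone analysed. At 10% left out the range is about 69% to 78%. These ranges rest on the assumed shares, on 3% being the control rate of the whole contact group, on contacts of suspected cases having a rate between 0% and 3%, and on no infections on treatment. The case for correction is the conflict over who is analysed, and it would hold even if power were unchanged.

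**What to change.** In Statistical models and methods of analysis, define the primary prevention population as all randomised women who were PCR-negative at recruitment and in contact with a confirmed or suspected case, analysed by ITT. Remove the word close, or define it and use it consistently in eligibility and study groups.

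Optionally, keep an analysis limited to contacts of confirmed cases as a pre-specified sensitivity analysis, with index-case status taken as recorded at randomisation so that the subset is fixed at baseline. That detail can sit in the SAP.

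The cost is one phrase in the Protocol and matching text in the SAP. Sample size, visits and study procedures do not change. The optional analysis needs index-case status to be recorded at randomisation.

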#### **Sample size**

A sample size of 100 infected pregnant women of each asymptomatic and symptomatic group, 1:1 randomly allocated into two study arms, allows to detect an effect size of 30%, 34% and 39% with 80% power and two-tail type-I error of 0.05 assuming 3%, 10% and 30% curation rates in the control group, respectively. In other words, this sample allows detecting differences if the cure rates in the intervention group are at least 33%, 44%, and 69%, respectively. A sample size of 257 non-infected, contact positive, pregnant women per intervention arm will be needed to detect a 3 % reduction in the prevalence of infection with 80% power and two-tail type-I error of 0.05, assuming a prevalence of infection in the control group of 3% after two weeks of follow up.

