#### **b) Treatment arm allocation**

Participants will be then randomized in a 1:1 ratio to HCQ (400 mg/day for three days, followed by 200 mg/day for 11 days) or placebo (2 tablets for three days, followed by one tablet for 11 days).

Allocation of participants to study arms will be done centrally by the trial's Sponsor (the Barcelona Institute for Global Health, ISGlobal) by block randomization. This method will ensure balanced allocation to both arms. The electronic CRF will assign automatically a study number to each participant, depending on her study group and recruitment site. Each number will be related to a treatment number, which assigns them to one of the study arms. Randomizations lists with treatment assignment for each study participant will be concealed in opaque sealed envelopes and only open in case of urgent need following study unblinding procedures.

A study card will be given to the participant in order to facilitate their clinical management in case they attend primary care centres or other hospitals.

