#### **d. Laboratory procedures**

##### **Detection of SARS-CoV-2 infection**

A Real-Time polymerase chain reaction (PCR) Coronavirus (COVID-19) assay diagnostic test will be performed at the lab study hospital for specific detection of SARS-CoV-2 viral RNA. Real-Time PCR technology utilizes polymerase chain reaction for the amplification of specific target sequences and target specific probes for the detection of the amplified RNA. The probes are labelled with fluorescent reporter and quencher dyes.

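### The primary Fisher test ignores recruitment site, although allocation appears to be blocked by study group and site; the test stays valid, but it is conservative and gives up some power in the infected groups

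*Protocol*

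**What the plan says.** Statistical models and methods of analysis fixes the primary test: "Proportions will be compared between the two intervention-arms within each group using the Fisher exact test". Its first comparison covers all women who were PCR positive at recruitment, without separating symptomatic from asymptomatic. The adjusted analysis follows: "Adjustment for co-variables and possible confounders will be done using Poisson regression with a log link and robust estimate of the covariance". No covariate is named, and the section does not say whether the adjusted or the unadjusted result is primary.

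Treatment arm allocation describes central block randomization. The electronic CRF gives each woman a study number "depending on her study group and recruitment site", and that number is tied to a treatment number. Trial design says participants are stratified by clinical presentation and PCR result, and does not mention site. Study sites lists five hospitals. Under Detection of SARS-CoV-2 infection, the PCR "will be performed at the lab study hospital".

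Sample size gives the infected groups as "A sample size of 100 infected pregnant women of each asymptomatic and symptomatic group, 1:1 randomly allocated into two study arms", "with 80% power and two-tail type-I error of 0.05 assuming 3%, 10% and 30% curation rates in the control group", with differences detectable "if the cure rates in the intervention group are at least 33%, 44%, and 69%, respectively".

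**The concern.** When allocation is balanced within a factor and that factor predicts the outcome, an analysis that leaves it out uses too large a variance. The error is on the safe side: the test rejects a true null less often than its nominal level and loses power. Site could be such a factor here, because each hospital recruits its own women and runs its own PCR. Fisher's exact test adds conservatism of its own in samples this small.

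The same issue arises for study group. If the word group in the primary analysis means all PCR-positive women, the pooled test also ignores symptomatic status, which Trial design names as a stratum.

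At stake is power in two groups of 50 per arm, should the true effect be smaller than the very large differences in Sample size. Analysing by the randomisation factors costs no patients.

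**Working it through.** **Inputs.** From the protocol: 100 women per infected group, 1:1, so 50 per arm; two-sided 0.05; control v intervention clearance of 3% v 33%, 10% v 44% and 30% v 69%; five hospitals, so 100/(2 × 5) = 10 women per arm per site if recruitment is even. Assumed: all between-site variation (the protocol gives none), and an odds ratio of 3.2 as a moderate effect. The protocol's pairs imply odds ratios of 15.9, 7.1 and 5.2; for example (0.69/0.31)/(0.30/0.70) = 5.19.

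**The plan's own figure.** Power = Φ{[|p1 − p0|√n − 1.96√(2p̄(1 − p̄))] / √(p0(1 − p0) + p1(1 − p1))}. For 30% v 69%, p̄ = 0.495.
- n = 50 per arm: (2.758 − 1.386)/0.651 = 2.107, power 98.2%.
- n = 25 per arm: (1.950 − 1.386)/0.651 = 0.867, power 80.7%.

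For the three pairs, power at 50 per arm is 98.3%, 97.8% and 98.2% by this formula, and 98.3%, 97.0% and 97.3% by exact Fisher enumeration. The stated 80% matches 25 per arm, not 50. That is a separate matter for Sample size; here it means there is little power left to gain at the stated effects.

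**Why site matters.** With equal arms inside each site, the pooled and stratified statistics share a numerator and differ only in variance. Take site control clearance of 10, 22.5, 35, 47.5 and 60%. The pooled variance factor is 0.35 × 0.65 = 0.2275. The average within-site factor is 0.35 − 0.15375 = 0.19625. The ratio is 0.863, so an unstratified Pearson test effectively uses 1.96/√0.863 = 2.11 as its cut-off, a true level of 3.5%. Simulation gave 3.4%.

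**Simulation.** 20,000 trials per scenario, 10 per arm per site, common odds ratio across sites, site rates evenly spaced over the range shown. Figures are percentages rejecting. MH is the site-stratified Mantel-Haenszel test; cc means with continuity correction.

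| Odds ratio | Site control clearance | Fisher | Pearson | MH, cc | MH, no cc |
|---|---|---|---|---|---|
| 1 | 30% at all | 3.2 | 5.1 | 2.9 | 5.1 |
| 1 | 20–40% | 3.0 | 4.7 | 3.0 | 4.9 |
| 1 | 10–60% | 1.9 | 3.4 | 2.8 | 5.0 |
| 1 | 30–90% | 1.6 | 3.1 | 2.9 | 5.1 |
| 3.2 | 30% at all | 76.4 | 82.4 | 76.1 | 82.4 |
| 3.2 | 20–40% | 74.4 | 80.4 | 74.5 | 80.5 |
| 3.2 | 10–60% | 62.9 | 71.1 | 66.6 | 74.4 |
| 3.2 | 30–90% | 51.8 | 60.4 | 57.5 | 66.8 |
| 5.19 | 30% at all | 97.4 | 98.4 | 97.3 | 98.4 |
| 5.19 | 20–40% | 96.8 | 98.0 | 96.8 | 98.0 |
| 5.19 | 10–60% | 91.9 | 94.7 | 93.3 | 95.6 |
| 5.19 | 30–90% | 82.0 | 87.3 | 84.6 | 90.1 |

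**Splitting the gain.** Fisher to Pearson is the cost of Fisher's conservatism; Pearson to MH without correction is stratification.
- Odds ratio 3.2: totals 6.0, 6.1, 11.5 and 15.0 points; stratification supplies 0.0, 0.1, 3.3 and 6.4.
- Odds ratio 5.19: totals 1.0, 1.2, 3.7 and 8.1 points; stratification supplies 0.0, 0.0, 0.9 and 2.8. In the last row control clearance averages 60%, so only the odds ratio, not the 30% control rate, is the protocol's.

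**Second check, overall rates held at the stated values.** With a standard deviation of 1 between sites on the log-odds scale, Fisher v MH without correction is 98.9 v 99.6 (3% v 33%), 98.0 v 99.3 (10% v 44%) and 98.2 v 99.2 (30% v 69%): gains of 0.7, 1.3 and 1.0. At effects where Fisher has about 80% power (3% v 23%, 10% v 35%, 30% v 59%), dropping Fisher gains 5–8 points without site differences, and stratification adds about 1–4 points at a standard deviation of 1.

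**Contact group.** 257 × 0.03 = 7.7 expected control infections and none expected on treatment, about 1.5 per hospital. There is little for stratification to recover.

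**The case against.** The strongest objection is that most of the gap is not about site. With no site differences there is nothing for stratification to recover, yet MH without correction still beats Fisher by 6 points, and an unstratified Pearson test recovers the same 6. This stands. A reader might infer that the whole 12–15 points comes from discarding the allocation structure; the split above does not support that.

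Second, blocking within site is inferred. The allocation section ties the study number to site but never says that blocks are formed within site, and Trial design omits it. This also stands, and it is why the first step is clarification.

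Third, between-site variation is not documented, and the laboratory section describes one assay, instrument and software version. Local testing therefore does not show that site is prognostic. Ranges of 10–60% or 30–90% across five hospitals are large. With 20–40%, stratification adds nothing.

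Fourth, covariate lists are commonly left to a statistical analysis plan, which is not at hand, and the robust Poisson model could carry site. That answers the missing covariate names. It does not answer the primary test, which the protocol itself fixes as Fisher.

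Finally, a reader might infer that the planned test is invalid or that the structure is wholly lost. Neither is supported: Fisher errs on the conservative side, strict control of type I error is a defensible aim, and comparison inside each group may well respect study group.

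**Conclusion.** The mismatch is real and worth correcting, but it is a matter of efficiency, not validity. The named primary test leaves out a factor on which allocation appears to depend. Whether it also leaves out symptomatic status turns on what group means.

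With 50 per arm, Fisher rejects a true null about 2–3% of the time at control clearance of 30% or more. At an odds ratio near 3 the recommended test gains about 6 points with no site differences, nearly all from dropping Fisher's conservatism. Under large assumed site differences it gains about 12–15 points, of which stratification contributes about 3–6. At the effects in Sample size the gain is about 1 point with little or no site variation; at an odds ratio of 5.2 it reaches about 4–8 points only under large assumed site differences. In the contact group it is small.

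The text and the direction of the effect are firm. The larger figures rest on assumed site differences, on an assumed odds ratio of 3.2 where that is used, and on even recruitment across sites.

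**What to change.** - In Treatment arm allocation, state whether recruitment site is a randomisation stratum, and bring Trial design into line.
- In Statistical models and methods of analysis, make the primary test in the infected groups a Mantel-Haenszel test without continuity correction, with a Mantel-Haenszel relative risk, stratified by site, and also by symptomatic status if the two infected groups are combined. Say which of these the word group means.
- Prespecify a rule for pooling sparse sites.
- Include site in the robust Poisson model.
- Keep Fisher as a sensitivity analysis. In the contact group Fisher may stay as primary.

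The cost is wording only, provided it is settled before unblinding. The downside is small: about 10 women per arm per site means some sites may need pooling, and the Mantel-Haenszel test is asymptotic where Fisher is exact. In the simulations above its null rejection was 4.9–5.1%.

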### **Secondary**

1. To determine the effect of HCQ on the clinical course and duration of the COVID-19 disease in SARS-CoV-2-infected pregnant women.
2. To determine the impact of HCQ on the risk of hospitalization and mortality of SARS-CoV-2-infected pregnant women.
3. To assess the safety and tolerability of HCQ in pregnant women.

4. To describe the clinical presentation of SARS-CoV-2 infection during pregnancy.
5. To describe the effects of maternal SARS-CoV-2 infection on pregnancy and perinatal outcomes by treatment group.
6. To determine the risk of vertical transmission (intra-utero and intra-partum) of SARS-CoV-2.

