#### *Infant*

1. Proportion of neonates with SARS-CoV-2- intrauterine infection by PCR-confirmed SARS-CoV-2-infection in nasopharyngeal aspirate.
2. Proportion of neonates with clinical signs/symptoms of COVID-19
3. Prevalence of low birth weight (<10th centile according to local standards) (21)
4. Prevalence of preterm birth (<37 weeks of gestational age)
5. Prevalence of embryo and foetal losses (miscarriages and stillbirths)
6. Frequency of congenital malformations
7. Proportion of adverse perinatal outcome
8. Neonatal morbidity
9. Neonatal mortality rate

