#### **Monitoring and reporting of Adverse Events**

Safety will be evaluated in the mother, the foetus and the newborn. Active safety monitoring will consist in daily phone visits to study participants from the initiation of treatment administration to assess drug tolerability and record all Adverse Events (AEs). In addition, a health facility-based passive surveillance system will be established to capture unscheduled visits of participants during follow-up.

The Principal Investigators (PI) at each study site will be responsible for recording, managing, and reporting of the AEs and SAEs as per study protocol. All AEs will be recorded in the AE form, and the DSMB will agree which SAEs and in what time frame will be reported.

All SAEs will be recorded on the SAE form and will be reported within 24 or 48 hours to the sponsor's (ISGlobal) Safety Coordinator, the CRO Dynamic Solutions, and to the DSMB as per study protocol. A flowchart will be provided to each study site to train the procedures for assessing AEs and reporting requirement according to severity and expectedness as well as persons responsible for recording and reporting of AEs/SAEs.

All participants enrolled in the trial will be educated at the beginning of the study on how to and whom to contact if they experience any untoward event and/or get admitted to the hospital.

In addition, Interim Safety Reports and Annual Safety Reports will be prepared by the Safety Coordinator and the CRO Dynamic Solutions and distributed to the local Ethic Committee, Sponsor, and DSMB as agreed in the study protocol.

The CRO Dynamic Solutions will ensure that AEs and SAEs are reported in compliance with International Conference on Harmonisation (ICH) Good Clinical Practice (GCP) guidelines and current international legislation during COVID-19 pandemic.

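### The protocol's general rule for proportions compares arms within each study group, which fits the PCR endpoints but leaves the pregnancy and infant endpoints split and without an overall estimate

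*Protocol*

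**What the plan says.** Three places in the protocol bear on this.

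- **Section 5.i, Statistical models and methods of analysis.** Two primary PCR comparisons come first: clearance in women positive at recruitment, and acquisition in negative contacts. The general rule follows: "Proportions will be compared between the two intervention-arms within each group using the Fisher exact test". Then: "Adjustment for co-variables and possible confounders will be done using Poisson regression with a log link and robust estimate of the covariance". No covariates are named, and study group is not mentioned among them. This is the only place that names a test for proportions.
- **Section 5.i, Statistical analysis populations.** For the Safety population: "The participant's safety will be analyzed by trial arm". There is no split by study group, and no test or estimate is named.
- **Section 5.e, Monitoring and reporting of Adverse Events.** "Safety will be evaluated in the mother, the foetus and the newborn".

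The Trial design section defines three study groups: symptomatic infected (100), asymptomatic infected (100) and PCR-negative contacts (514). Women are randomised within each group, and the Treatment arm allocation section sets the ratio at 1:1. The secondary endpoints include preeclampsia, growth restriction, preterm birth, embryo and foetal loss, malformations and neonatal outcomes. Secondary objective 3 is undivided: "To assess the safety and tolerability of HCQ in pregnant women".

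**The concern.** A within-group comparison is right for the PCR endpoints, because they mean different things in different groups: clearance in infected women, acquisition in contacts. It is a poor choice for pregnancy and infant outcomes. Whether two weeks of hydroxychloroquine changes the risk of preterm birth or pregnancy loss is one question, whatever the woman's PCR result at entry.

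Under the general rule that question gets separate answers from groups of very unequal size, and no overall effect estimate or confidence interval. Because the Safety population text can be read the other way, the protocol also does not settle which foetal and newborn outcomes are pooled. That choice could then be made after results are known.

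**Working it through.** **Group sizes (Trial design; Sample size).** 100 + 100 + 514 = 714. At 1:1 this is 50 + 50 + 257 = 357 per arm.

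**The plan's own figure.** The contact group is sized for 3% v 0%, 80% power, two-sided 0.05. With pooled variance under the null (mean risk 0.015) and no continuity correction:

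n = [1.96·√(2·0.015·0.985) + 0.8416·√(0.03·0.97 + 0)]² / 0.03² = (0.3369 + 0.1436)² / 0.0009 ≈ 256.5, so 257 per arm.

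This matches the protocol. The 257 was chosen for infection, not for pregnancy outcomes.

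**Precision lost by splitting.** With similar risks in all groups, the standard error of a risk difference scales as 1/√n. Relative to 357 per arm:
- 50 per arm: √(357/50) = 2.67 times larger
- 100 per arm: √(357/100) = 1.89 times larger
- 257 per arm: √(357/257) = 1.18 times larger

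**Power.** The protocol gives no control risks for pregnancy or infant outcomes, so the risks below are assumptions. The Fisher columns are exact two-sided power at 0.05 by enumeration. The last column is a Mantel-Haenszel test without continuity correction, simulated with strata of 50, 50 and 257 per arm.

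| Assumed risk, placebo v HCQ | Fisher, 50/arm | Fisher, 100/arm | Fisher, 257/arm | Fisher, 357/arm pooled | Stratified M-H |
|---|---|---|---|---|---|
| 2% v 4% | 0.6% | 4% | 18% | 28% | 35% |
| 2% v 6% | 3% | 17% | 58% | 75% | 80% |
| 5% v 10% | 6% | 19% | 53% | 68% | about 72–73% |
| 5% v 12% | 12% | 34% | 79% | 91% | 93% |
| 7% v 14% | 11% | 29% | 70% | 84% | 87% |

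The stratified test keeps its size: 4.5% to 5.0% when both arms have a risk of 2%, 5% or 10%. Most of its small gain over pooled Fisher comes from omitting the continuity correction. With the correction, its power at 5% v 10% is 68%, the same as pooled Fisher.

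**Chance that every within-group test is non-significant.** The groups are independent, so for three groups it is (1 − power at 50)² × (1 − power at 257):
- 5% v 10%: 0.937² × 0.474 = 42%
- 5% v 12%: 0.880² × 0.213 = 16%
- 7% v 14%: 0.889² × 0.302 = 24%
- 2% v 6%: 0.968² × 0.422 = 40%
- 2% v 4%: 0.994² × 0.815 = 81%, but here the pooled Fisher test also has only 28% power

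With two PCR-status groups, 5% v 10% gives (1 − 0.190) × (1 − 0.526) = 38%.

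**The case against.** The strongest reply is that the protocol does not confine every comparison to the study groups. Safety has its own population and its own by-arm rule, and safety is said to cover mother, foetus and newborn. Adverse events, and arguably malformations, losses and neonatal events, could already be analysed by arm across all women. This stands. A reader might infer that the protocol only ever compares arms within groups, and the text does not support that. But the by-arm sentence names no estimate or stratification. The pregnancy and infant outcomes are listed as secondary endpoints, which the general rule reaches.

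Second, the rule directly follows the PCR bullets and may have been meant for them alone. Its wording does not say so, and no other rule for proportions exists.

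Third, the three-way split is a reading. The first primary bullet takes infected women together ("among those women who were SARS-CoV-2 PCR positive at recruitment in the ITT and ATP cohorts"), which suggests 100 v 100 and 257 v 257. This stands as an alternative and softens the loss, but 19% power at 5% v 10% is still poor.

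Fourth, these outcomes are secondary, and secondary objective 5 is worded as descriptive. So no confirmatory claim is at risk. A descriptive aim still needs an overall estimate.

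Fifth, the section gives the analysis in general terms and a separate plan is to follow, where stratification terms commonly sit. Their absence here would not be a finding. The point is that the protocol states a rule, and the rule does not suit these endpoints.

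Last, pooling is no rescue for modest effects: at 5% v 7.5%, exact Fisher power with 357 per arm is only 23%.

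**Conclusion.** The point holds as a cheap improvement to the choice of analysis and a needed reconciliation of two sections. As written, the general rule for proportions splits the binary pregnancy and infant endpoints by study group and gives no overall estimate, while the Safety population text points to comparison by arm.

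At an assumed 5% v 10%, power is 6% in each infected group (19% if they are combined) and 53% in contacts, against 68% pooled or about 72–73% stratified. Compared with the contact group alone the gain is moderate. The larger losses are the near-uninformative infected-group tests and the missing overall estimate.

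A reader might go further and infer that a real harm would probably appear as three non-significant results. The figures do not support that as a general statement. In the scenarios with pooled power of 68% or more, it happens in 16% to 42% of trials. It becomes likely only for effects that the pooled test would usually miss as well.

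All power figures rest on assumed risks, equal across groups, with complete follow-up.

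**What to change.** In Statistical models and methods of analysis:

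1. Limit the within-group comparison to the PCR and COVID-19 efficacy endpoints, and say whether the groups are the three study groups or the two PCR-status groups.
2. State, consistently with the Safety population text, that pregnancy, infant and adverse-event outcomes are compared by arm across all women, stratified by study group. Use a Mantel-Haenszel relative risk and risk difference with confidence intervals, or the planned robust Poisson model with study-group terms.
3. Show group-specific results and an arm-by-group interaction as supportive.

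The cost is wording only. No new data or participants are needed, and the comparison keeps the randomisation because allocation is 1:1 within group. The downside is that a single summary assumes a common relative effect across groups. The interaction display checks this, though with 50 per arm in each infected group it will detect only large differences.
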